### Data collection and statistical analysis

Participants will fill an online form reporting all clinical and intra-operative data of each patient who will undergo a laparoscopic appendectomy. All personal information of patients will be removed according to data anonymization.

Data will be reported in accordance with Strengthening the Reporting of Observational studies in Epidemiology guidelines (STROBE) for observational studies [22].

Residents from each involved center will be responsible for data collection.

All forms will be collected in an electronic database by the coordinating residents who will check for data completeness. All residents taking part in the study will be asked to enter eventual missing data.

The incidence of IAA after laparoscopic appendectomy reported in the literature ranges from 1.5 to 20% [4, 5, 9–11]. Such a wide interval is not negligible when calculating the sample size (*n*) of the study cohort. Furthermore, some important basic considerations need to be taken into account: appendicitis is the most common acute surgical disease so the baseline population is large and cannot be exactly estimated; the incidence of intra-abdominal abscesses has never been systematically investigated in regard to the severity of appendicitis and contamination. All patients included in the study will be classified into different clusters considering the grade of appendicitis and contamination, lavage vs suction alone, and postoperative incidence of IAA.

Considering all these aspects, sample size for power calculation can be reasonably estimated given a 95% confidence interval with a *z*-score of 1.96, a 50% standard deviation, and a 0.03 margin of error. This formula does not include the incidence rate of IAA for the aforementioned reasons.

The estimated sample size would be around at least 1067 patients. Data will be collected in a computerized spreadsheet (Microsoft Excel 2016; Microsoft Corporation, Redmond; WA) and analyzed with statistical software (IBM Corp. Released 2017. IBM SPSS Statistics for Windows, version 25.0. Armonk, NY).

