*χ*^*2*^ test will be assessed to compare categorical variables, and univariate logistic regression will be performed to provide hazard ratios for individual variables, identifying possible predictors of postoperative complication (IAA above all). All significant (*p* < 0.05) variables at univariate analysis will be included in a multivariate regression model in order to detect independent risk factors for the outcome and to estimate odds ratio and 95% confidence intervals.

A scoring system will be built according to the results of statistical analysis. The weight of each variable will be addressed based on odds ratio values. To evaluate the accuracy of the score, discrimination and calibration of the model will be explored. The former will be assessed by receiver operating characteristic (ROC) curve analysis, whereas the latter will be investigated with the Hosmer-Lemeshow goodness-of-fit test. Based on the results of the ROC curve analysis, we will proceed to identify different severity grades of acute appendicitis each one related to a specific risk of developing delayed IAA. *χ*^*2*^ test will be assessed to compare categorical variables, and univariate logistic regression will be performed to provide hazard ratios for individual variables, identifying possible predictors of postoperative complication (IAA above all). All significant (*p* < 0.05) variables at univariate analysis will be included in a multivariate regression model in order to detect independent risk factors for the outcome and to estimate odds ratio and 95% confidence intervals.

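### The score's AUC is to be taken in the cohort that builds the score, with no optimism correction named, so it is expected to be too high, most of all if abscesses are rare

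*Protocol article*

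**What the plan says.** All of this is in the Protocol article, Data collection and statistical analysis.

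- Selection: significant "variables at univariate analysis will be included in a multivariate regression model in order to detect independent risk factors".
- Score: "A scoring system will be built according to the results of statistical analysis", and "The weight of each variable will be addressed based on odds ratio values".
- Accuracy: "To evaluate the accuracy of the score, discrimination and calibration of the model will be explored". For discrimination: "The former will be assessed by receiver operating characteristic (ROC) curve analysis". Calibration is left to the Hosmer-Lemeshow test.
- Size: "The estimated sample size would be around at least 1067 patients", obtained "given a 95% confidence interval with a *z*-score of 1.96, a 50% standard deviation, and a 0.03 margin of error". The section says that the event rate was deliberately left out of this formula.
- Event rate: "The incidence of IAA after laparoscopic appendectomy reported in the literature ranges from 1.5 to 20" per cent.

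The article describes a single cohort. It mentions no split sample, bootstrap, cross-validation or external validation cohort, and it gives no expected AUC and no count of candidate variables.

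**The concern.** An AUC computed in the same patients who decided which variables enter and what weight each receives is biased upward on average, because selection and weighting both fit chance features of that cohort. The bias grows as events become fewer relative to the candidates screened. Here the sample size ignores the event rate, so the number of events could be very small while the list of recorded items is long.

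The AUC is the figure by which surgeons would judge whether the score separates low from high risk. The Discussion calls classifying patients and creating the score the core step, and the Conclusions expect practical consequences from applying it. An uncorrected AUC could make a weak score look serviceable.

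**Working it through.** **1. The plan's own figure.** n = z² × 0.25 / margin² = 1.96² × 0.25 / 0.03² = 0.9604 / 0.0009 = 1067.1. The stated 1067 is reproduced.

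**2. Events, from the article's IAA range.**
- 1.5%: 0.015 × 1067 = 16
- 5%: 0.05 × 1067 = 53
- 10%: 0.10 × 1067 = 107
- 20%: 0.20 × 1067 = 213

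**3. Candidate parameters (assumed from the items listed in Methods and Table 1).** Four appendix aspects give 3 df. Six contamination types plus an assumed level for none give 6 df. Fourteen further items are counted at 1 df each: age, sex, BMI, ASA class, Charlson index, PIRO, Alvarado, CRP, lavage, lavage volume, drainage, operative time, operator and difficulty. The total is 3 + 6 + 14 = 23 df. At 1.5% IAA there are fewer events (16) than candidate parameters (23).

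**4. Simulation of the stated rule.** Each cohort had n = 1067 and 23 candidate df. Variables were screened by univariate likelihood-ratio test at p < 0.05 and entered in a multivariable logistic fit. Optimism = AUC in the cohort − AUC of the same fitted rule in 60,000 new patients. Cohorts in which nothing passed the screen were dropped, since they give no score to report. Predictor prevalences and effects are assumptions. There were 120 cohorts per cell for the fitted model and 200 for the point score. The point score used rounded odds-ratio weights, with continuous items split at the median; its ranges cover keeping all screened variables or only the independently significant ones.

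Mean optimism:

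| Rule and assumed signal | 1.5% | 5% | 10% | 20% |
|---|---|---|---|---|
| Fitted model, none | 0.193 | 0.108 | 0.081 | 0.062 |
| Fitted model, modest (true AUC about 0.64) | 0.199 | 0.109 | 0.068 | 0.047 |
| Fitted model, strong (about 0.74) | 0.197 | 0.079 | 0.038 | 0.028 |
| Point score, none | 0.174–0.183 | 0.098–0.107 | 0.071–0.076 | 0.051–0.054 |
| Point score, modest | 0.164–0.190 | 0.093–0.105 | 0.062–0.067 | 0.042–0.044 |
| Point score, strong | 0.149–0.188 | 0.071–0.075 | 0.043–0.045 | 0.029–0.031 |
| Point score, very strong (about 0.81) | 0.118–0.167 | 0.057 | 0.038–0.040 | 0.018–0.019 |

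For example, with modest signal at 1.5% the fitted model shows 0.732 in its own cohort and 0.533 in new patients. With strong signal at 10% it shows 0.752 and 0.714.

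**5. Cross-checks under other assumptions.** A separate simulation used the 9-df classification plus 12 other candidates, two of them real (21 df if each counts as one), with 250 cohorts per rate. It gave mean optimism of 0.202 at about 1.4% IAA, 0.093 at about 5% and 0.057 at about 10%. A further simulation with 23 df gave 0.15–0.20 at 1.5%, 0.05–0.12 at 5%, 0.03–0.08 at 10% and 0.02–0.07 at 20%.

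**6. Combined range.** About 0.12–0.20 at 1.5%, 0.05–0.12 at 5%, 0.03–0.08 at 10% and 0.02–0.07 at 20%. Mean optimism was positive in every scenario.

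**7. The condition matters.** In step 4 no variable passed the screen in 40–54% of no-signal cohorts. For the fitted model at 1.5% IAA this happened in 20% of modest-signal and 8% of strong-signal cohorts. The figures describe studies that end up with a score.

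**The case against.** The strongest reply is that this is silence, not error. The article does not say that an uncorrected AUC will be the headline and does not rule out internal validation, a detail that a condensed article may leave to a fuller document. Part of this stands: same-sample evaluation is inferred from the single cohort and is not stated in words. But the article sets out the whole chain and names its accuracy measures, and following those steps gives an apparent AUC.

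The size is also open to challenge. A reader might infer that the AUC will certainly be inflated by a set amount, or that inflation is never below about 0.06. The documents do not support that. They give no effects and no candidate count; at 10% IAA with strong signal the optimism is about 0.04, and at 20% it can be about 0.02. The Introduction reports associations of IAA with perforation, BMI, leukocytosis and operative time, so a no-signal scenario should not be taken as the expected case. The 1067 is also a minimum, and a larger cohort would reduce the bias.

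A reader might also infer that the plan would test the fitted model and never the score. That is too literal: the same sentence names the score's accuracy as its target.

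Finally, the AUC is not the primary endpoint, and the article looks ahead to further studies. This limits the point's importance without removing it.

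**Conclusion.** The concern holds in this form: with one cohort described and no correction named, the ROC analysis as planned gives an apparent AUC that is expected to be too high. The direction is secure. The size depends on the event rate, the true signal and the number of candidates, of which the documents give only a range for the first. It runs from serious at 1.5% IAA (about 0.12–0.20) to small at 20% (about 0.02–0.07). These are means over simulated cohorts with at least one selected variable, at n = 1067 and about 20–23 assumed candidate df.

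That a nearly uninformative score would pass as useful is a possibility at low event rates with weak signal, not a prediction. The point concerns the AUC as a reported figure; it makes no claim about the calibration test or the grade cut-offs. It should be changed before analysis, but it does not put the study itself in question.

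**What to change.** State that the headline measure of discrimination is the AUC of the final point score, corrected for optimism by bootstrap with at least 500 resamples:

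1. In each resample repeat the whole sequence: univariate screening, multivariable fit and point assignment.
2. Take the AUC of that resample's score in the resample and in the original cohort; the difference is its optimism.
3. Count a resample that selects nothing as a constant score (AUC 0.5), so that it is not silently dropped.
4. Subtract the mean optimism from the apparent AUC, and report the corrected value with a 95% confidence interval.

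A leave-one-hospital-out AUC may be added as support only, and it should pool the held-out predictions across hospitals. The Discussion describes a network of 27 hospitals. If all took part equally, 16 events would be 16 / 27 = 0.6 per hospital and, under a Poisson assumption, about e^(−0.6) = 55% of hospitals would have none, so no AUC could be computed there.

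The cost is a short analysis script and no new data. The downside is a less favourable AUC.

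### The only calibration check named for the score is a Hosmer-Lemeshow test, apparently run in the data that built it, where it cannot show overfitting

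*Protocol article*

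**What the plan says.** All of this is in the Protocol article, section Data collection and statistical analysis.

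- Selection: significant "variables at univariate analysis will be included in a multivariate regression model", with significance set at p < 0.05.
- Score: "A scoring system will be built according to the results of statistical analysis", and "The weight of each variable will be addressed based on odds ratio values".
- Purpose of the check: "To evaluate the accuracy of the score, discrimination and calibration of the model will be explored".
- Discrimination: "The former will be assessed by receiver operating characteristic (ROC) curve analysis".
- Calibration: "the latter will be investigated with the Hosmer-Lemeshow goodness-of-fit test". The "Hosmer-Lemeshow goodness-of-fit test" is the only calibration method named.
- Use: the ROC results serve to "identify different severity grades of acute appendicitis each one related to a specific risk of developing delayed IAA".

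The section describes a single cohort of at least about 1067 patients. It mentions no data split, resampling, shrinkage or second sample.

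**The concern.** The score is meant to attach an absolute IAA risk to each grade, and the Discussion treats creating it as the central step of the study. Calibration is the property that says whether such risks hold in later patients. Selection on univariate p-values, followed by weights from the same fit, tends to make predictions too extreme. A goodness-of-fit test in the fitting data does not look for that: it compares the model with the data to which it was adjusted. If this test is the only calibration evidence, the report could show a reassuring p-value beside risks that are too high in the top grades and too low in the bottom ones.

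**Working it through.** **The plan's own figure.** n = z² × p(1 − p) / d² = 1.96² × 0.25 / 0.03² = 0.9604 / 0.0009 = 1067.1. The stated 1067 reproduces. The article gives no figure for how the calibration test performs, so that was simulated.

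**Why the test cannot see overfitting.** Maximum-likelihood logistic regression solves Σ(y − p) = 0 and Σx(y − p) = 0 for every predictor x in the model. The linear predictor is a sum of these terms, so Σ LP(y − p) = 0 as well. Regressing the outcome on LP in the same data therefore returns intercept 0 and slope 1 exactly. The test can still reveal wrong functional form. Adding noise variables does not create that kind of misfit.

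**Inputs from the article.** N = 1067; IAA incidence 1.5 to 20%; univariate p < 0.05, then a multivariable model.

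**Assumptions.** Twenty candidate predictors; Hosmer-Lemeshow with up to 10 groups, df = groups − 2, level 0.05 (the article states no level for this test). Twenty is not excessive. The Methods list 8 clinical variables and 6 operative ones, and Table 1 has four appendix aspects (3 indicators) and six contamination types (5 indicators): 8 + 6 + 3 + 5 = 22.

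**Simulation 1.** Half binary and half continuous predictors, 500 runs per scenario, true slope taken in 50,000 new patients. Runs that selected no variable drop out. HL = Hosmer-Lemeshow test.

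| Incidence | Events (1067 × incidence) | Mean events per tenth | HL pass, same data: no real effects / four real effects | Median slope in new patients, four effects | AUC apparent / new, four effects | HL pass in 1067 new patients, four effects |
|---|---|---|---|---|---|---|
| 1.5% | 16.0 | 1.6 | 96.2% / 94.3% | 0.35 | 0.71 / 0.57 | 51.0% |
| 3% | 32.0 | 3.2 | 96.3% / 95.7% | 0.46 | 0.68 / 0.59 | 54.9% |
| 5% | 53.4 | 5.3 | 94.9% / 96.4% | 0.64 | 0.67 / 0.61 | 65.6% |
| 10% | 106.7 | 10.7 | 95.8% / 94.2% | 0.82 | 0.67 / 0.64 | 73.2% |
| 20% | 213.4 | 21.3 | 95.4% / 95.6% | 0.86 | 0.67 / 0.64 | 77.6% |

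The same-data pass rate does not move as the true slope goes from 0.35 to 0.86. It also stays at about 95% for models with no real signal (new-data AUC 0.50, slope about 0). The smallest same-data cell has 196 runs, so its simulation error is √(0.05 × 0.95 / 196) = 1.6 percentage points. With all-binary predictors the pass rate was 98 to 100% for the model, and 95 to 100% for a rounded odds-ratio score refitted to the same data, among runs with at least three risk groups.

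A slope of 0.64 means the fitted log odds ratios are too large by a factor of 1 / 0.64 = 1.56; at 0.86 the factor is 1 / 0.86 = 1.16.

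**Simulation 2: strength of the effects.** Five real effects among 20 candidates, 150 runs per scenario, incidence 3 / 5 / 10 / 20%. Log odds ratio 0.4 per predictor gave median slopes of 0.50 / 0.66 / 0.76 / 0.86; log odds ratio 0.9 gave 0.84 / 0.90 / 0.91 / 0.94. Further runs down to 1.5% gave about 0.3 to 0.7 (1.5 to 5%) and 0.77 to 0.86 (10 to 20%) under modest effects, and about 0.7 to 0.95 overall under strong effects.

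**Sparse groups.** With five real effects, an average of 8.3, 6.1 and 2.6 of 10 deciles had under 5 expected events at 3, 5 and 10% incidence. At 20% the count was 0.0 under modest effects and 2.2 under strong ones.

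**Effect on grade-level risk.** Observed IAA incidence in the top model-defined third, development data against new patients, modest signal:

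- 3% incidence: 5.5 − 4.2 = 1.3 points
- 5%: 8.7 − 7.8 = 0.9 points
- 10%: 16.9 − 15.4 = 1.5 points
- 20%: 32.0 − 30.3 = 1.7 points

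With strong signal the differences were 1 point or less.

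**The case against.** **The document does not say what the concern needs.** The article never states that the test is run in the development data, sets no pass rule, and only says that calibration will be explored. The grades come from the ROC analysis, not from this p-value. A reader might infer that a non-significant result will certify the score; the text does not say so, and that inference should not be charged to the plan. Same-data testing is also an inference, but a firm one, because no other sample is described.

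**A condensed article may leave validation to a fuller document.** True, so the absence of a bootstrap is not in itself the point. What stands is that the article does name a calibration method, for a stated purpose, and the method does not serve that purpose.

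**The size is assumption-driven.** This stands. The number of candidates and their effects are not in the protocol. With strong predictors the slope is often 0.84 or higher, and the article itself cites perforation as a reported risk factor.

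**Sparse deciles.** A reader might infer that most risk groups would be too sparse for the test. That holds only at about 5% incidence or below, and the article's range reaches 20%.

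**Harm to the grades.** A reader might infer that published grade risks would be badly wrong. Where this was computed, the bias has the expected direction but is modest. Thirds stand in for the plan's ROC-based grades, whose cut-points are not yet known.

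**The root cause is the univariate selection, not the test.** Correct. The point here is narrower: the named check would not reveal the consequence.

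**Conclusion.** The point holds as a worthwhile and cheap improvement. As the only calibration check named, and applied as far as the text shows to the cohort that built the score, the Hosmer-Lemeshow test rejects about 5% of the time whatever the overfitting. It therefore says almost nothing about whether the risks attached to the grades will hold in new patients. That conclusion needs only same-data testing and a 0.05 level. The size is conditional on 20 candidates and on the assumed effects: it is substantial at low incidence with modest effects and small at 20% incidence or with strong effects. The cohort's data remain fully usable.

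**What to change.** In Data collection and statistical analysis, replace the Hosmer-Lemeshow test as the calibration criterion. It may stay as a descriptive check for misfit. Suggested content:

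- Draw bootstrap samples and repeat the univariate selection, model fit and scoring in each.
- Report the optimism-corrected calibration slope and intercept and the corrected AUC, with a calibration plot.
- Multiply the log odds ratios by the corrected slope before assigning points.
- Report observed IAA risk with a 95% CI for each grade.

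In a simulated check, the bootstrap with selection repeated estimated a slope of 0.71 against a true 0.77 at 5% incidence, and 0.83 against 0.84 at 10%. The true values in that check are somewhat above the 0.71 and 0.81 medians from the parent runs (five real effects, 400 studies per incidence), a difference I cannot account for. I take from it only that the method exposes the overfitting and may slightly overcorrect.

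The cost is a change of wording and some scripting, in or outside the SPSS version the article names. No new data are needed. Reported performance will look less favourable.

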**Methods:**

Patients suffering from acute appendicitis will be enrolled during a 1-year period, according to inclusion and exclusion criteria. Participants will fill an online form reporting all clinical and intra-operative data of each patient undergoing a laparoscopic appendectomy. General surgery residents will be responsible for data collection. Our proposal of classification is based on the histological grade of appendicitis and intra-operative degree of peritoneal contamination. For each grade, a progressively increasing score is assigned.

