## Hypothesis, design of the study, and aims

The driving hypothesis of our study is that there should exist a relationship between different intra-operative treatment protocols (irrigation vs suction alone) and postoperative incidence of IAA. Furthermore, considering various grades of appendicitis and peritoneal contamination, the use of irrigation vs suction alone could lead to different rates of postoperative IAA.

The aim of this study is to introduce and evaluate a classification for acute appendicitis taking into account the peritoneal contamination to delineate the relationship between grade of appendicitis and postoperative incidence of IAA considering the surgeon’s attitude toward irrigation or suction alone. Some studies described that the incidence of postoperative IAA is higher in the perforated appendix [12, 13]. No clear evidence exists exploring the severity of peritonitis as a potential predictor of IAA and its relationship with irrigation or suction alone.

This is a prospective observational multicenter study.

Primary endpoint:Relationship among each severity grade of acute appendicitis and postoperative incidence of intra-abdominal abscesses

Secondary endpoint:Impact of intraperitoneal irrigation or suction alone on the incidence of IAA for each severity grade

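### Severity grade has two conflicting meanings; if the primary endpoint uses the ROC-derived one, the exposure is built from the outcome and its IAA risks and AUC are optimistic

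*Protocol article*

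**What the plan says.** All references are to the Protocol article.

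- **Primary endpoint** (Hypothesis, design of the study, and aims): "Relationship among each severity grade of acute appendicitis and postoperative incidence of intra-abdominal abscesses". The secondary endpoint, irrigation against suction alone, is also to be examined within each severity grade.
- **Grade fixed in advance.** The Abstract (Methods) bases the classification on histology and intra-operative contamination and adds: "For each grade, a progressively increasing score is assigned". The Methods section lists the grade under this classification among the intra-operative findings. Table 1 gives four appendix aspects and six contamination types, with one of each per patient.
- **Grade derived from the data** (Data collection and statistical analysis). Variables are screened against the outcome: "All significant (*p* < 0.05) variables at univariate analysis will be included in a multivariate regression model". Then: "A scoring system will be built according to the results of statistical analysis". And: "The weight of each variable will be addressed based on odds ratio values". The last step is the grading itself: "Based on the results of the ROC curve analysis, we will proceed to identify different severity grades of acute appendicitis". The same sentence goes on to tie every such class to its own probability of a later abscess.
- **Performance** (same section): "To evaluate the accuracy of the score, discrimination and calibration of the model will be explored", by ROC curve and Hosmer-Lemeshow test.

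**The concern.** The article uses one term for two different things. The first is a category read from the operation and the histology. The second is a class whose ingredients, weights and cut-offs are all chosen because they separate patients with IAA from those without, in the cohort in which grade and IAA are then related.

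On the second definition, a relation between grade and IAA is largely guaranteed by construction, and the IAA rate per class and the AUC are too favourable. The Abstract (Discussion) promises risk classes with a specific IAA incidence for each, so those rates are a main product of the study. The secondary endpoint inherits the same grades. Lavage is one of the recorded operative variables and nothing keeps it out of the score, so the grade could also absorb part of the effect it is meant to stratify.

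**Working it through.** **1. The plan's own figure.** n = z²p(1−p)/E² = 1.96² × 0.5 × 0.5 / 0.03² = 0.9604 / 0.0009 = 1067.1, which reproduces the stated 1067. It is a precision calculation for one proportion and this point does not change it. It serves below as N.

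**2. Inputs.** From the article: N = 1067, screening at p<0.05, the sequence of screening, multivariable model, odds-ratio weights and ROC-based grades, and an IAA incidence of 1.5% to 20%. Assumed, because the article does not give them: the number of candidates (5, 10 or 20 independent binary variables, prevalence 15% to 50%; or only Table 1, as 3 aspect and 6 contamination indicators with assumed frequencies), and a single Youden cut.

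**3. No predictor related to IAA** (2000 runs per scenario, IAA 1.5%, 5%, 10% and 20%). A score exists if at least one candidate passes the screen. For K independent candidates this probability is 1 − 0.95^K.

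| Candidates | 1 − 0.95^K | Simulated: score exists |
|---|---|---|
| 5 | 22.6% | 21–24% |
| 10 | 40.1% | 37–41% |
| 20 | 64.2% | 61–64% |
| Table 1 only | not independent | 33–35% |

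Given a score, the ROC-cut grade was related to IAA at p<0.05 in the same patients in 99.4% to 100% of runs. The overall false-positive rate is the product of the two, so it is almost equal to the last column.

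Two comparisons locate the cause:
- Score and cut frozen, then tested in 1067 new patients: 2.6% to 7.3% significant, given a score.
- The four Table 1 aspects, fixed beforehand, in one chi-square test: 4.0% to 5.1%.

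So the inflation comes from deriving the grade from the outcome and relating it to that outcome in the same patients. The spurious contrast is visible: with 20 noise candidates, mean IAA in the high and low grade is 7.4% and 3.3% at 5% incidence (apparent AUC 0.60), and 3.0% and 0.7% at 1.5% incidence (apparent AUC 0.68). The true AUC is 0.50.

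**4. Some predictors real.** Assumed: three binary predictors with odds ratios 3, 2.5 and 2, plus 7 or 17 noise variables, N = 1067.

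| IAA | AUC apparent | AUC true | High/low grade, apparent | High/low grade, true |
|---|---|---|---|---|
| 5% | 0.71–0.72 | 0.67–0.68 | 10–11% / 2.4–2.6% | 9% / 3.0–3.2% |
| 10% | 0.71 | 0.69 | not used | not used |

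The AUC is inflated by about 0.02 to 0.04 (0.72 − 0.67 = 0.05 at the extreme). At 5% IAA the risk ratio between grades appears as about 10/2.5 = 4 where the truth is about 9/3 = 3.

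**The case against.** - **A sound reading exists.** The grade listed among the intra-operative findings is the Table 1 category. The statistical section speaks of clustering patients by grade of appendicitis and contamination, and it opens its analysis with tests of individual variables. On that reading the primary analysis uses categories set before the outcome, and the simulated error rate is about 5%. This stands. A reader might infer that the primary endpoint is circular as a matter of fact; the article supports only that it is ambiguous, and circular on one of its two definitions.
- **No test of the derived grades is written.** The chi-square sentence after the ROC sentence repeats the start of the same section word for word and looks like a copying slip. This stands. A reader might infer that the trial's type I error is 64%. That would be the error rate of an unstated test under the highest of several assumed candidate counts.
- **A global null is implausible.** The article itself cites perforation, body mass index, leukocytosis and long operative time as associated with IAA. This stands, and it makes optimism, not false discovery, the main practical harm.
- **Building risk classes from outcome data is what score development does, and validation detail may sit in a fuller document.** This stands in part. Missing validation detail is not the finding. The finding is that the article calls the product of score development by the name of the primary exposure. A fuller document could add an optimism correction, but it could not keep both definitions.

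**Conclusion.** The point holds as a conflict of definitions with a measurable consequence. Severity grade is fixed in advance in the Abstract, Methods and Table 1, and derived from IAA in the statistical section; the primary endpoint does not say which it means. Under the second definition a relation with IAA is almost certain once a score exists, and the overall false-positive rate under a complete null is roughly 20% to 64%, depending on an assumed 5 to 20 independent candidates. Under the more realistic case of some true predictors, the relation is real but overstated, to the extent shown in the second table. Those figures rest on assumed odds ratios, candidate counts and a single cut. The direction does not: performance and class risks measured in the patients who built the classes are biased in the favourable direction.

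**What to change.** 1. State that the primary endpoint is analysed on the Table 1 categories as recorded before the outcome is known. Use a prespecified global test with appendix aspect and contamination as categorical factors.
2. Use a trend test only where an order is declared in advance: the article states none between abscess and peritonitis types. If the full table has no level for patients without contamination, give them their own.
3. Call the ROC-derived classes by another name and make them a secondary, model-development product. Reconcile the Abstract's statement on increasing scores with the odds-ratio weights.
4. Report AUC, calibration and IAA risk per class corrected for optimism, by a bootstrap that repeats screening, weighting and cut-off selection, or by leaving centres out in turn. Give no p-value for derived class against IAA in the development data.
5. State which grade the irrigation comparison uses; the Table 1 categories avoid the same problem there.

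The cost is wording, some extra analysis and computing time, and a less favourable AUC and risk gradient. No further patients or variables are needed for the change itself. At the lowest cited incidence, 1067 × 0.015 = 16 events would be spread over many categories, so the global test would then have little information; that limit belongs to the sample, and deriving the grades from the same events would not remove it.
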